### Power analysis

Pre-existing datasets showing the relationship between prehospital NIRS oximetry values and patient injury outcomes in the context of TBI are lacking. To answer Aim 1, a sample size of 242 subjects with severe TBI will provide 90% power to detect correlation of 0.22 or higher [33] in a 2-sided 0.05 level test of the null hypothesis of no correlation between NIRS cerebral oximetry values and admission Glasgow Coma Score (GCS) adjusting for 29 (approximately 12%) unsuccessful NIRS monitoring data collection attempts (25) in a time series based regression analysis. CareFlight’s historical mission database indicates 1210 total recruits will be required to incorporate 242 subjects with severe TBI.

To address Aims 2 and 3, the same number of subjects will be enough to show an incidence of EGOS 4 at six months post-injury of 56% (95%CI 49% to 63%) and demonstrate a clinically important change in EGOS of 1 point associated with NIRS cerebral oximetry value at 80% power to detect a Cochrane-Armitage test for trend in EGOS groups (30% deceased, 20% poor neurological outcome and 50% good neurological outcome) at significance level of 0.05. The expected proportion of EGOS groups have been taken from the subject characteristics from the Head Injury Retrieval Trial [data under analysis] [29].

As for validation of the model for Aims 2 and 3, we will internally validate the models using bootstrapping methods on 1000 samples.

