### Subgroups for analysis and reporting

Some patients, particularly those with more severe injuries and those of a different age, are more likely to have monitor findings indicating strong associations with outcomes and are therefore of particular interest. Subgroup analysis will be undertaken on patients with severe TBI (first GCS ≤ 12 and Abbreviated Injury Score (Head) ≥ 3), severe traumatic injury (ISS > 15), and paediatric patients (age < 16 years).

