#### Statistical analysis for aim 3: associations with long-term outcomes

Utilising the same groupings for NIRS tissue oximetry (NIRS 1 through 3), associations with EGOS (grouped into EGOS < 2, 2–4 and 5–8), GOS and CANS will be tested with the same multivariate analyses and ordinal logistic regression approach described above. This will include adjustment for ISS, age, sex and other covariates. For validation of the model for Aims 2 and 3, we will internally validate the models using bootstrapping methods on 1000 samples. All data analysis will be performed using SPSS version 21 and STATA 13.1 software (StataCorp, College Station, TX).

### Outcomes for aim 3

This analysis will establish simple associations between NIRS cerebral oximetry values and the subsequent long-term functional recovery of patients with TBI. This would potentially allow early identification of patients with more severe injuries to optimise early intervention and engagement of rehabilitation services.

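### The 80% power stated for Aims 2 and 3 belongs to a trend test and a 1-point EGOS effect that do not correspond to the planned analyses, so it is unsupported

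*Protocol article*

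**What the plan says.** Under Power analysis, the protocol sizes Aim 1 first: "a sample size of 242 subjects with severe TBI will provide 90% power to detect correlation of 0.22 or higher", with an allowance for 29 failed recordings. It then carries the number over: "To address Aims 2 and 3, the same number of subjects will be enough". The claim for Aims 2 and 3 is that these subjects suffice to "demonstrate a clinically important change in EGOS of 1 point associated with NIRS cerebral oximetry value at 80% power". The test is a "Cochrane-Armitage test for trend in EGOS groups (30% deceased, 20% poor neurological outcome and 50% good neurological outcome) at significance level of 0.05".

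The analysis sections read differently:

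- **Aim 2.** Three NIRS groups are formed from the area at or below 45%: none, up to the median, above the median. Kruskal-Wallis checks the grouping. Chi-square tests relate the groups to imaging findings, mortality and survival to discharge. A proportional-odds model then adjusts for ISS, age, sex and further covariates entered stepwise, with NIRS 1 as the reference group.
- **Aim 3.** The protocol says that "associations with EGOS (grouped into EGOS < 2, 2–4 and 5–8), GOS and CANS will be tested with the same multivariate analyses", using the same ordinal regression.

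A yes/no classification of cerebral desaturation (at least one episode of one minute) is defined under Aim 2, but no named analysis uses it.

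**The concern.** A power figure describes a particular test of a particular effect. Here neither matches the plan.

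- **Test.** Cochran-Armitage needs one binary variable against ordered groups. The plan crosses three NIRS groups with three EGOS groups and adjusts for covariates.
- **Effect.** It is stated as one point on an eight-level scale, but the scale analysed has three levels.
- **Aim 2.** The figure is claimed for Aims 2 and 3 together, although none of the Aim 2 outcomes is EGOS.

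The 80% is the stated justification of sample size for the long-term question. If readers take it as the power of the Aim 3 analysis, a null result could be read as evidence against an association that the study may have had little chance of detecting.

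**Working it through.** **1. The companion figures reproduce, and they fix the sample size.** Evaluable patients: 242 − 29 = 213.

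- Correlation, Fisher z: atanh(0.22) × √(213 − 3) − 1.96 = 0.2237 × 14.49 − 1.96 = 1.28, which is 90% power, as stated.
- Proportion of 56%: 0.56 ± 1.96 × √(0.56 × 0.44 / 213) = 49.3% to 62.7%, as stated (49% to 63%). With 242 it would be 49.7% to 62.3%.

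So 213 is the number behind the stated figures.

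**2. The 80% cannot be reproduced.** No effect is given on the scale of the test. For a two-sided Cochran-Armitage test with EGOS groups of 30/20/50% and 213 patients, 80% power needs an odds ratio per EGOS group of 2.11, 1.73, 1.61 or 1.56 if 10%, 20%, 30% or 50% of patients desaturate (assumed shares). Nothing in the protocol links any of these to one EGOS point. Reading one point as one whole collapsed group gives power of 0.99 or more, so that reading does not return 80% either.

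**3. What the collapsed scale registers.** Eight levels have seven adjacent steps. With groups 1, 2–4 and 5–8, only the steps 1/2 and 4/5 cross a boundary; the other five do not.

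**4. Power for a 1-point effect under assumptions.** The protocol gives neither the eight-level distribution nor the exposed share (NIRS 2 or 3). I assumed three distributions that all collapse to 30/20/50% (levels 1 to 8, in %):

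- A, even within groups: 30; 6.7, 6.7, 6.7; 12.5 four times
- B, mass near the 4/5 cut: 30; 2, 6, 12; 20, 14, 9, 7
- C, mass away from the cuts: 30; 5, 10, 5; 4, 10, 16, 20

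The test is a two-sided Mann-Whitney at 0.05, exposed against unexposed, n = 213, 6,000 simulated trials per setting. It stands in for an unadjusted two-group proportional-odds test. Three-group power:

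| Effect | Distribution | 10% exposed | 20% | 30% | 50% |
|---|---|---|---|---|---|
| Proportional-odds shift, mean 1 point | A (OR 2.03) | 40% | 61% | 72% | 78% |
| | B (OR 2.18) | 45% | 69% | 80% | 87% |
| | C (OR 1.92) | 33% | 54% | 65% | 72% |
| Survivors lose 1 point, no added deaths | A | 10% | 16% | 18% | 22% |
| | B | 19% | 33% | 41% | 48% |
| | C | 6% | 6% | 6% | 7% |

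The survivor-only effect averages less than one point over all patients, because the deceased cannot move.

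On all eight levels the ranges are about 34–88% (proportional-odds shift) and 15–58% (survivors only). The information under proportional odds, 1 − Σp³, is 1 − (0.027 + 0.008 + 0.125) = 0.84 for three groups against about 0.96 for eight, a ratio of about 0.87.

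**5. What the planned type of model can detect.** Take EGOS group as outcome and NIRS as predictor, unadjusted. For a score x = 0, 1, 2, log OR per step = √(λ / (213 × 0.84/3 × Var(x))), where 213 × 0.84/3 = 59.64. For 80% power at two-sided 0.05, λ = 7.85 on 1 df (linear score) and 9.63 on 2 df (three-level factor, true effect still equal per step).

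| NIRS 1/2/3 split | Var(x) | OR per step, linear score | OR per step, three-level factor |
|---|---|---|---|
| 50/25/25 | 0.6875 | 1.55 | 1.62 |
| 80/10/10 | 0.41 | 1.76 | 1.87 |
| 90/5/5 | 0.2275 | 2.14 | 2.32 |

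First row: √(7.85 / (59.64 × 0.6875)) = 0.4375, and exp(0.4375) = 1.55.

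**The case against.** The strongest defence is that sizing on a simpler related test is common. The protocol does define a binary desaturation variable, so its trend across ordered EGOS groups is a coherent Cochran-Armitage set-up. The three groups in the power statement (deceased, poor, good) appear to match the Aim 3 groups. The test is close to the score test of an unadjusted logistic model. This stands as far as it goes: the figure could roughly stand in for an unadjusted Aim 3 analysis with NIRS dichotomised. It does not cover three NIRS groups, covariate adjustment or any Aim 2 outcome, and it leaves the 1-point effect unconnected to the test.

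A reader might infer that true power is below 80%. The documents do not support that. They give no exposure share and no eight-level distribution. Distribution B reaches 80% at 30% exposed and 87% at 50%. If one point is lost per NIRS step across three groups, a linear trend on the collapsed groups reaches 0.85–0.88 with that distribution and 40% or more desaturated.

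A reader might also infer that collapsing EGOS causes most of the problem. Under a proportional-odds shift it costs little. It matters when the loss is confined to survivors, and even then the full scale does not restore 80%.

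Nor is it a contradiction that severe TBI appears under the subgroup heading ("Subgroup analysis will be undertaken on patients with severe TBI"). All three aims concern TBI, and the total of 1,210 is set to yield 242 severe cases. An exposure share missing from a condensed article is likewise no error in itself; it matters here because any restated power figure needs one.

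**Conclusion.** The point holds in this form: the 80% is unsupported for the Aim 2 and Aim 3 analyses as written. The mismatch of test, the mismatch of effect scale and the absence of EGOS from Aim 2 follow from the protocol's text and need no assumption.

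The size does rest on assumptions: 213 evaluable patients, three invented EGOS distributions, 10–50% exposed, and an unadjusted two-group comparison. On these, ten of twelve proportional-odds settings fall short of 80%, one sits at it and one exceeds it; all twelve survivor-only settings fall short. These figures show how far power could lie from 80%. They are not a corrected value.

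The illustrative odds ratios are also unadjusted and take EGOS as the outcome. The Aim 2 wording lists injury type as an independent variable, which read literally makes NIRS group the response. The mismatch with Cochran-Armitage remains either way.

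**What to change.** 1. Replace the 80% statement for Aim 3 with the power, or the minimum detectable odds ratio, of the planned proportional-odds model in the 213 evaluable severe-TBI patients. State the assumed NIRS 1/2/3 split, whether NIRS enters as a linear score or a three-level factor, and which variable is the response. The odds ratios in the last table of the working show the form; they would need the sponsor's own split.
2. Drop the 80% claim for Aim 2.
3. Either drop the 1-point wording, or add an analysis of the full eight-level EGOS so that a 1-point change can register. The added analysis should not be presented as restoring 80% power.

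The cost is wording, plus one further analysis if the second option in item 3 is taken. No extra patients or data are needed. The downside is that the stated figure becomes less favourable.

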### Subgroups for analysis and reporting

Some patients, particularly those with more severe injuries and those of a different age, are more likely to have monitor findings indicating strong associations with outcomes and are therefore of particular interest. Subgroup analysis will be undertaken on patients with severe TBI (first GCS ≤ 12 and Abbreviated Injury Score (Head) ≥ 3), severe traumatic injury (ISS > 15), and paediatric patients (age < 16 years).

### Data analysis

#### Novel analysis methodology to address aim 1: establishing new analysis methods

A variety of approaches to signals analysis as commonly utilised in biomedical engineering fields will be undertaken. These will include (but not be limited to) time series analysis and pattern recognition and classification undertaken on all monitoring value streams (StO_2_, HbT, HbO_2_ and HbD) for each of the cerebral probes separately, and the peripheral reference probe. These may be matched to ancillary signals including peripheral oxygen saturation and electrocardiograph parameters (RR and QT intervals, RR variability). Comparison may also be made between NIRS oximetry probes. Control group patients with traumatic injuries but no brain injury will be the reference group for analysis of “standard” signals analysis patterns comparisons.

#### Novel analysis methods applied to acute phase outcomes

Analyses undertaken in this way will be tested against the following changes seen on cerebral imaging: no intracranial pathology, intracerebral lesions (haemorrhage or contusion), subdural haematoma, extradural haematoma, traumatic subarachnoid haemorrhage and diffuse injury. Comparison to 24 hour and 30 day mortality will also be undertaken. Control group patients with traumatic injuries but no brain injury will provide data for analysis of “standard” signals analysis patterns.

#### Novel analysis methods applied to long-term outcomes

Analysis as described above will also be assessed against long-term outcomes as grouped by EGOS score at 6 and 12 months as described in the statistical analysis (EGOS < 2, 2–4 and 5–8).

### Outcomes for aim 1

Exploration of a variety of signals analysis approaches to analyse NIRS cerebral oximetry is an explicit component of the study design. Establishment of useful approaches of this nature offer the greatest chance to develop real-time non-invasive monitoring that reflects the underlying pathology that is developing. This has implications not just for future management relevant to all prehospital practitioners but may inform better approaches to utilising NIRS cerebral oximetry in hospital care.

#### Statistical analysis for aim 2: associations of nirs tissue oximetry with acute phase outcomes

The area under the curve for cerebral oximetry value ≤ 45% (minutes x desaturation points ≤ 45%) will be used as an independent variable for statistical analyses as described previously [34]. Patients with one or more episodes of cerebral oximetry value ≤ 45% for 1 minute will be classified as experiencing a decline in cerebral oxygen saturation.

We will define 3 NIRS cerebral oximetry patient groups:NIRS 1 (cerebral oximetry values remain > 45% i.e. area under the curve = 0 min%).NIRS 2 (cerebral oximetry values ≤ 45% for > 0 min up to the median area under the curve for cerebral oximetry value ≤ 45% to be determined).NIRS 3 (cerebral oximetry values ≤ 45% for more than the median area under the curve for cerebral oximetry value ≤ 45% to be determined).

The total duration (minutes) of StO_2_ ≤ 45%, longest duration (minutes)

StO_2_ ≤ 45%, minimum and average StO_2_ will be derived for each patient. These variables will be compared between NIRS 1, NIRS 2 and NIRS 3 groups using Kruskal-Wallis analysis of variance to check the validity of this grouping.

A chi-square test will be used to assess the association between cerebral oximetry values by comparing patients in each of the above groups in their association with the following injury patterns on cerebral imaging: no intracranial pathology, intracerebral lesions present, subdural haematoma, extradural haematoma, traumatic subarachnoid haemorrhage and diffuse injury. The same analysis will also be repeated to establish associations with 24 hour and 30-day mortality and survival to discharge.

In the multivariate analysis, an ordinal logistic regression under a proportional odds model with NIRS 1 as the reference group will be used with the six types of injury on cerebral imaging listed above included as an independent variable after adjusting for ISS, age, sex and other covariates (mean arterial pressure, first recorded GCS, peripheral oximetry, end-tidal CO_2_, HbT) in a stepwise fashion. A score test will be used to verify the proportional odds assumption in the final model. The unadjusted and adjusted odds ratios and 95% confidence intervals will be reported. Significance will be set at P < 0.05.

### Outcomes for aim 2

This analysis will establish the associations between NIRS cerebral oximetry values and types of brain injury. This will underpin new approaches to interpretation of NIRS tissue oximetry values to provide real-time information corresponding with the development of pathology underlying the cerebral oximetry probes, be that swelling and oedema or acute development of blood collections.

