### Study design and setting

This is a prospective cohort study.

This research will be conducted in a prehospital emergency medical service employing a physician-paramedic model of care to deliver rapid response trauma care and employing both rotary-wing and road transport modalities. The clinical team is capable of providing advanced life support, anaesthesia, intubation and ventilation, blood transfusion and peripheral haemorrhage control manoeuvres along with other critical care interventions at the scene of the accident or during patient transport.

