### Monitor application

For the purposes of this research, NIRS cerebral oximetry will be applied by a trained researcher as soon as possible after arrival at the patient to ensure the clinical team are able to undertake their standard approach to care. The monitor employed will be a Nonin EQUANOX 7610 Regional Oximetry monitor (TM Nonin Medical, Inc.). This trained observer will apply monitoring probes bifrontally to the forehead of patients and to a peripheral reference site on the forearm (Figure 1). Monitoring will be commenced within a time frame of 30 minutes after the initial injury. The monitoring screen will only show that data capture is proceeding with warning signals if there are issues with sensor contact or signal quality. The EQUANOX 7610 monitor will continuously store the NIRS monitoring data. NIRS monitoring will cease on patient handover at the receiving hospital.

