### Patient event and intervention marking

The data capture system for the NIRS oximetry monitor will also facilitate real-time marking of clinical events and interventions by the study observer. This will include real-time marking of bag-mask ventilation, cardiopulmonary resuscitation, anaesthesia with thiopentone, anaesthesia with ketamine, intubation, institution of mechanical ventilation, administration of vasopressor, transfusion, administration of hypertonic saline and seizure activity. Study observers will also have the ability to mark other potential events deemed clinically relevant. This will provide accurate information on interventions undertaken in a manner that is time-matched to the NIRS oximetry monitoring data. Event marking will be combined with NIRS oximetry monitoring data and general observations monitoring to allow reporting of standard interventions and care as previously described [26]. Patient general observations monitoring information and management and intervention details will be presented in conjunction with all outcome data.

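### CPR time stays in the StO2 exposure although it is marked in real time, so the unadjusted mortality comparisons could reflect cardiac arrest rather than brain injury

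*Protocol article*

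**What the plan says.** All references are to the protocol article.

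- **Exposure** (Statistical analysis for aim 2). The area under the curve at or below 45% "will be used as an independent variable for statistical analyses as described previously". NIRS 1 has zero area. NIRS 2 and NIRS 3 lie below and above the median area. Aim 3 reuses these groups for EGOS, GOS and CANS.
- **Recording period** (Monitor application). Probes go on as soon as possible after arrival, and "NIRS monitoring will cease on patient handover at the receiving hospital". No section limits the area to part of this period.
- **Care given in that period** (Study design and setting). "The clinical team is capable of providing advanced life support, anaesthesia, intubation and ventilation, blood transfusion", at the scene or in transit.
- **Event marks** (Patient event and intervention marking). "This will include real-time marking of bag-mask ventilation, cardiopulmonary resuscitation, anaesthesia with thiopentone", followed by further airway, drug and transfusion events, all time-matched to the NIRS data. The stated use is reporting of interventions and presentation beside the outcomes.
- **Eligibility** (Inclusion and exclusion criteria). Cases without a trauma mechanism are excluded. Traumatic cardiac arrest is not.
- **Tests** (Statistical analysis for aim 2). Chi-square tests, without adjustment, for imaging patterns, 24-hour and 30-day mortality and survival to discharge. The ordinal models adjust for ISS, age, sex, mean arterial pressure, first GCS, peripheral oximetry, end-tidal CO2 and HbT, in a stepwise fashion.

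**The concern.** While circulation has stopped, cerebral StO2 can be expected to be low whatever the state of the brain, and the risk of death is high. A patient monitored during CPR therefore tends to bring both a large area under the curve and a death. If enough such patients sit in NIRS 3, the mortality tables will show a gradient even if StO2 carries no information about brain injury in anyone else.

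The article intends the Aim 2 results to support real-time information on pathology under the probes, and the Aim 3 results to identify patients for early intervention and rehabilitation. An association carried by cardiac arrest serves neither purpose. The information needed to separate the two explanations is already captured, but the plan gives it no analytic role in Aims 2 and 3.

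**Working it through.** **1. Evaluable patients.** The Power analysis gives 242 severe TBI patients, "adjusting for 29 (approximately 12%) unsuccessful NIRS monitoring data collection attempts". Its figure reproduces with the Fisher z formula: n = ((1.960 + 1.282) / atanh(0.22))² + 3 = 213.06, and 213 + 29 = 242. So 213 evaluable patients are used. The sample size is not in dispute.

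**2. Assumptions.**
- Half the patients never fall to 45%, and the median split halves the rest: 107/53/53. The share that desaturates is not in the documents.
- Mortality outside arrest is 30% in every group, from the expected outcome split "30% deceased, 20% poor neurological outcome and 50% good neurological outcome". This means no StO2-death association outside arrest.
- k arrest patients are all in NIRS 3 and all die. The documents do not give k.

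**3. Expected NIRS 3 mortality** = (k + 0.30 × (53 − k)) / 53, against 30% in NIRS 1 and NIRS 2:
- k = 5: 19.4/53 = 36.6%
- k = 10: 22.9/53 = 43.2%
- k = 15: 26.4/53 = 49.8%
- k = 20: 29.9/53 = 56.4%

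**4. Chi-square on the expected table** (3×2, 2 degrees of freedom, critical value 5.99).
- k = 10: deaths 32.1, 15.9 and 22.9, overall 70.9/213 = 0.333. The contributions are 0.52 + 0.26 + 2.35 = 3.13, below the critical value.
- k = 15: deaths 32.1, 15.9 and 26.4, overall 74.4/213 = 0.349. The contributions are 1.14 + 0.57 + 5.16 = 6.87, above it.

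**5. Simulated rejection at 0.05**, deaths drawn as binomials:

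| Arrest patients k (share of 213) | All in NIRS 3, all die | 80% in NIRS 3, rest in NIRS 1, 90% die |
|---|---|---|
| 0 | 5% | 5% |
| 5 (2.3%) | 10% | 7% |
| 10 (4.7%) | 32% | 15% |
| 15 (7.0%) | 66% | 29% |
| 20 (9.4%) | 93% | 49% |

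With 25% instead of 30% mortality outside arrest, the middle column becomes 12, 39, 78 and 97% for k = 5 to 20.

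**6. Sensitivity to the desaturation share.** A second simulation held overall mortality at 30%, formed the groups by the median rule, and gave the arrest patients large areas and certain death. With 8 to 10 arrest patients, rejection was 93 to 99.5% if 10% of the others desaturate, 58 to 83% if 20% do, and 28 to 45% if 40% do. With 5 arrest patients it was 46, 24 and 13%. The rarer desaturation is, the smaller NIRS 3 is and the more each arrest counts.

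**The case against.** **A condensed article leaves sensitivity analyses to the full plan, and the quoted sentence refers to a cited method.** This is partly right: a statistical analysis plan may contain such an analysis. But the article itself fixes the exposure, groups, tests and named covariates, and those choices as written include CPR time. A reader might infer that the event marks are barred from analysis. The text does not say that; it states a reporting use and is silent on any other.

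**Rejection here is not a type I error.** This stands. In the simulated cohort StO2 and death really are associated, through arrest. The objection is to reading that association as one of brain injury. A cumulative area over the monitored period remains a defensible description of total insult, so the planned analysis should stay.

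**The covariates may absorb the effect.** ISS, first GCS, mean arterial pressure, peripheral oximetry and end-tidal CO2 are plausible markers of arrest, so the adjusted models are less exposed. How much less was not tested. Stepwise selection does not guarantee that these terms stay, and the mortality chi-square tests have no adjustment.

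**The premises come from outside the documents.** This stands for the number of arrests, their StO2 and their mortality. The requirements of transport by the team and later follow-up consent may also keep the number small.

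**Treatment could hide a true association.** A reader might infer this from the pooling of time before and after anaesthesia or ventilation. The documents give no effect of these treatments on StO2, so no size can be attached to it.

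**Conclusion.** The point holds as a question of interpretation, mainly for the unadjusted comparisons of NIRS 1 to 3 with 24-hour mortality, 30-day mortality and survival to discharge. It holds to a lesser and untested extent for the adjusted EGOS models.

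Under the 107/53/53 layout with 30% mortality, 5 to 20 arrest patients give 10 to 93% rejection in the extreme case, and 7 to 49% if 80% of them are in NIRS 3 and 90% die. The true size cannot be determined, because neither the arrest rate nor the desaturation share is documented.

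Two stronger readings are not supported. First, it does not follow that a few arrests are enough to create the association in the grouped test: in this layout 5 patients barely move it, and they matter more only if desaturation is assumed to be rare. Second, nothing shows that the imaging comparison is distorted; arrest patients who die before imaging do not enter it.

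This is a cheap improvement, not a fault that invalidates the plan.

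**What to change.** Keep the planned whole-recording analysis. Pre-specify that every Aim 2 and Aim 3 analysis is repeated:

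1. excluding patients with marked prehospital CPR; and
2. with CPR-marked time removed from all StO2 measures (area, durations, minimum and average), with the NIRS groups formed again.

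State in advance that a NIRS-outcome association will be interpreted as TBI-related only if it persists in these repeats. Report the number of patients with CPR and their NIRS group, so that readers can judge their weight.

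A split before and after the first airway or anaesthesia event may be added as exploratory only. The area should then be expressed per monitored minute, because an area in minutes depends on window length. Patients without such an event should be analysed on their whole recording, because they have no split point.

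The cost is extra analysis of data already captured, with slightly fewer patients and somewhat lower precision in the repeats. For example, removing 10 of 213 patients leaves 203. Sample size, data collection and patient care do not change.

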## Discussion

The ideal prehospital monitoring technology for the patient with TBI would be a non-invasive monitor that provides real-time information regarding conditions in the brain tissue. Appropriately validated this would provide the treating clinician as to what the organ needs at that moment to decrease the size of acute injuries and enhance patient recovery in the long term.

NIRS tissue oximetry may provide such an option. It is easy to apply without delay. In the hospital setting good sensitivity has already been demonstrated for detection of intracranial haematomas preoperatively when correlated with CT or MRI [16-18]. Correlation with invasive monitoring has shown mixed results. Increased length of time with an StO_2_ below 60% has been associated with intracranial hypertension, decreased cerebral perfusion pressure and mortality in a small observational study [33]. In this study, monitoring was applied at the time of cerebral imaging, but this occurred anywhere up to twelve hours after the initial insult.

Research comparing regional oxygen saturation to direct, invasive brain tissue oxygen tension in 22 patients for the 16 hours after severe traumatic brain injury showed moderate accuracy in detecting severe brain hypoxia with area under curve on receiver-operating characteristic curve of 0.82 (with a likelihood ratio of a positive test of 5.3) but a poor ability to detect moderate hypoxia [19]. In this study patients had already passed the phase where they required resuscitation, and had all received neurosurgery. As a result many hours had passed and the subsequent monitoring and analysis is not reflective of early stage pathology.

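### Aims 2 and 3 test outcomes only through three oximetry groups, so every patient who stays above 45% counts as the same; a continuous StO2 term, already derived, should be prespecified alongside

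*Protocol article*

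**What the plan says.** The section on the statistical analysis for Aim 2 opens with a continuous quantity: "The area under the curve for cerebral oximetry value ≤ 45% (minutes x desaturation points ≤ 45%) will be used as an independent variable". It then sets out the classes: "We will define 3 NIRS cerebral oximetry patient groups". The first is "NIRS 1 (cerebral oximetry values remain > 45% i.e. area under the curve = 0 min"%, that is, no reading at or below the cut. The second covers any positive AUC "up to the median area under the curve for cerebral oximetry value ≤ 45% to be determined", and the third covers AUC above that median.

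The tests named for Aim 2 use these classes. They are a chi-square test against imaging findings, mortality at 24 hours and 30 days and survival to discharge, and a proportional odds model with NIRS 1 as reference. Aim 3 begins "Utilising the same groupings for NIRS tissue oximetry (NIRS 1 through 3") and applies the same approach to EGOS, GOS and CANS.

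The Aim 2 section also says that total and longest duration at or below 45%, and "minimum and average StO_2_ will be derived for each patient". Their one stated use is a comparison between the groups "using Kruskal-Wallis analysis of variance to check the validity of this grouping".

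The Discussion reports that "Increased length of time with an StO_2_ below 60% has been associated with intracranial hypertension", and also with lower cerebral perfusion pressure and with mortality, in a small observational study.

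**The concern.** The section on NIRS monitoring data has StO2 recorded every 4 seconds. Aims 2 and 3 turn that record into one of three labels. A patient held just above 45% for the whole transport and a patient who never leaves the normal range both enter as NIRS 1. Yet the article itself cites an association for time spent below 60%, a cut under which these two patients could differ.

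Two summaries that separate such patients, average and minimum StO2, are already computed. They go only into a check of groups that were built from the same readings, which says little about whether the grouping captures what matters for outcome.

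What is at stake is sensitivity. If outcome varies with StO2 over its range, the named tests could miss or understate an association that the recorded data could show. If outcome varies only with the burden at or below 45%, little is lost. The document does not say which holds, so resting every named test on the second case is an avoidable restriction.

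**Working it through.** **Inputs from the Power analysis section.** Target correlation 0.22, two-sided 0.05, 90% power, 242 subjects with severe TBI, of whom 29 (about 12%) are expected to have failed monitoring. Evaluable: 242 − 29 = 213.

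**The plan's own figure.** By Fisher's z, n = ((1.960 + 1.282) / atanh 0.22)² + 3 = 213.06. This agrees with 213, and power at n = 213 is 0.900. The figure is stated for Aim 1, for a correlation of oximetry values with admission GCS. It is borrowed below only as a scale for comparison. The 80% power stated for Aims 2 and 3 (Cochran-Armitage trend) cannot be recomputed, because neither the spread of the exposure nor the group shares are given.

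**Assumptions, not in the document.** The StO2 summary is normally distributed, it relates linearly to outcome, and a share d of patients reaches 45% or below. d is varied from 10% to 50%.

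**Information kept by a three-group trend (scores 0, 1, 2).** NIRS 1 has share 1 − d; NIRS 2 and NIRS 3 have d/2 each. With cuts c1 = Φ⁻¹(1 − d) and c2 = Φ⁻¹(1 − d/2):

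- covariance of score and exposure = φ(c1) + φ(c2)
- variance of score = 2.5d − (1.5d)²
- information kept = covariance² / variance

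Worked for d = 30%: c1 = 0.524, c2 = 1.036; covariance = 0.3477 + 0.2332 = 0.5809; variance = 0.75 − 0.2025 = 0.5475; kept = 0.3374 / 0.5475 = 0.616.

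Power = Φ(atanh(0.22 × √kept) × √210 − 1.96). For d = 30%: 0.22 × √0.616 = 0.1727; atanh = 0.1744; × 14.49 = 2.528; minus 1.96 = 0.568; power = 0.715.

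| Share reaching 45% | Information kept | Equivalent n (of 213) | Power, trend | Power, 2 df |
|---|---|---|---|---|
| 10% | 0.341 | 73 | 0.465 | 0.382 |
| 20% | 0.506 | 108 | 0.628 | 0.534 |
| 30% | 0.616 | 131 | 0.715 | 0.623 |
| 50% | 0.747 | 159 | 0.797 | 0.711 |

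The continuous summary has power 0.90 in every row. The 2-df column treats the three groups as unordered categories.

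**The opposite case.** Suppose the effect runs only through the burden at or below 45%, with AUC zero for most patients and lognormal otherwise. The squared correlation of the group score with log(1 + AUC) is then 0.93–0.96, a loss of about 4–7%. A log-mean of 3 and log-SD of 1 give values in this range; a wider spread of AUC loses more.

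**Would AUC alone repair the loss?** No. Under the same normal, linear assumption, AUC as a linear predictor gives power 0.383, 0.555, 0.664 and 0.789 in the four rows, no better than the three-group trend, because it is also zero for everyone above 45%. Using the ordered AUC values as the dependent variable in a proportional odds model changes the information kept only from 0.347 to 0.349, 0.507 to 0.516, 0.615 to 0.633 and 0.745 to 0.794. Only a summary that varies above 45%, such as average or minimum StO2, recovers the rest.

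**The case against.** The strongest reply is that the three groups are a deliberately simple layer. Under Aim 1 the article applies signals analysis to all the streams and tests the results against imaging, mortality and EGOS. Its study plan says these methods will offer better options for Aims 2 and 3. So a reader should not infer that the study throws away the continuous record. This stands in part. But the Aim 1 work is openly exploratory with an open list of methods, and it does not replace the named Aim 2 and 3 tests.

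The opening AUC sentence might also be read as promising a continuous predictor. No test described afterwards uses it that way, and AUC would still be zero for everyone above 45%.

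The power figures are borrowed. They do not show that Aims 2 and 3 fall short of their own 80%, and they describe a trend or 2-df test on a linear scale, not the chi-square test or the proportional odds model.

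Four stronger readings are tempting and are not supported:

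- *That the 60% study is the only TBI evidence described.* The Discussion also covers haematoma detection and a 22-patient comparison with brain tissue oxygen, which found moderate accuracy for severe hypoxia and poor ability to detect moderate hypoxia. That comparison gives some support to a low threshold. The article also cautions that hospital evidence cannot be transferred directly.
- *That readings below 60% fall almost wholly in NIRS 1.* NIRS 1 is a class of patients, not a range of values, and patients with long spells below 60% may also reach 45%.
- *That a median cut cannot be used elsewhere.* Once determined, it is a fixed value that another cohort can apply.
- *That NIRS 2 and 3 would be almost empty.* About 11 patients each at 10% desaturating (213 × 0.05) applies to the severe TBI subgroup. On all 1210 recruits with 12% failed monitoring (about 1065) it is about 53 each.

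**Conclusion.** The point holds as a limitation of the named Aim 2 and 3 analyses. They rest on three groups that cannot distinguish among patients who stay above 45%, while two continuous summaries that can are derived and not used against any outcome in those aims.

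The size depends on facts that the document does not contain. If outcome relates linearly to a normally distributed StO2 summary, the groups keep about a third to three quarters of the information as the share desaturating goes from 10% to 50%. If the effect lies only in the burden at or below 45%, the loss is about 4–7% under the lognormal assumption used. This does not make the grouped analysis invalid, and it does not show the study to be underpowered. It shows a plausible and possibly large loss of sensitivity that can be avoided with data already in hand.

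**What to change.** Keep NIRS 1–3 and the AUC at or below 45% as the planned descriptive threshold analysis. Add, prespecified for Aims 2 and 3:

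1. Average StO2 (or minimum; name one in advance) as a continuous predictor.
2. AUC at or below 45% as an any/none indicator plus log AUC among those with a positive value, which deals with the many zeros without grouping.
3. Both in models where the acute outcomes and EGOS, GOS and CANS are the dependent variables, with the planned adjustment for ISS, age, sex and the other covariates.
4. Area below 60%, from the same stored readings, as one sensitivity exposure.

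Do not rely on ordered AUC as the dependent variable to solve this, since it leaves everyone above 45% tied.

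The change is to analysis wording only: no new patients and no new measurements. The cost is a little more analysis and results that are less simple to present than three groups.
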